## Abstract

**Background:**

Breast reconstruction is an integral part of breast cancer care. There are 2 main types of breast reconstruction: alloplastic (using implants) and autologous (using the patient’s own tissue). The latter creates a more natural breast mound and avoids the long-term need for surgical revision—more often associated with implant-based surgery. The deep inferior epigastric perforator (DIEP) flap is considered the gold standard approach in autologous breast reconstruction. However, complications do occur with DIEP flap surgery and can stem from poor flap tissue perfusion/oxygenation. Hence, the development of strategies to enhance flap perfusion (eg, goal-directed perioperative fluid therapy) is essential. Current perioperative fluid therapy is traditionally guided by subjective criteria, which leads to wide variations in clinical practice.

**Objective:**

The main objective of this trial is to determine whether the use of minimally invasive cardiac output (CO) monitoring for guiding intravenous fluid administration, combined with low-dose dobutamine infusion (via a treatment algorithm), will increase tissue oxygenation in patients undergoing DIEP flap surgery.

**Methods:**

With appropriate institutional ethics board and Health Canada approval, patients undergoing DIEP flap surgery are randomly assigned to receive CO monitoring for the guidance of intraoperative fluid therapy in addition to a low-dose dobutamine infusion (which potentially improves flap oxygenation) versus the current standard of care. The primary outcome is tissue oxygenation measured via near-infrared spectroscopy at the perfusion zone furthest from the perforator vessels 45 minutes after vascular reanastomosis of the DIEP flap. Low dose (2.5 μg/kg/hr) dobutamine infusion continues for up to 4 hours postoperatively, provided there are no associated complications (ie, persistent tachycardia). Flap oxygenation, hemodynamic parameters, and any medication-associated side effects/complications are monitored for up to 48 hours postoperatively. Complications, rehospitalizations, and patient satisfaction are also collected until 30 days postoperatively.

**Results:**

Funding and regulatory approvals were obtained in 2019, but the study recruitment was interrupted by the COVID-19 pandemic. As of October 4, 2023, 34 participants have been recruited. Because of the significant delays associated with the pandemic, the expected completion date was extended. We expect the study to be completed and ready for potential news release (as appropriate) and publication by July 2024. No patients have suffered any adverse effects/complications from participating in this study, and none have been lost to follow-up.

**Conclusions:**

CO-directed fluid therapy in combination with a low-dose dobutamine infusion via a treatment algorithm has the potential to improve DIEP flap tissue oxygenation and reduce complications following DIEP flap breast reconstruction surgery. However, given that the investigators remain blinded to group randomization, no comment can be made regarding the efficacy of this intervention for improving tissue oxygenation at this time. Nevertheless, no patients have been withdrawn for safety concerns thus far, and compliance remains high.

**Trial Registration:**

Clinicaltrials.gov NCT04020172; https://clinicaltrials.gov/study/NCT04020172

## Introduction

### Background

Over the last several decades, breast reconstruction has evolved to become an integral part of breast cancer care. In many countries, including Canada, access to breast reconstruction has become a quality indicator for breast cancer care [1]. There are 2 main types of breast reconstruction: alloplastic (ie, using implants), and autologous (ie, using the patient’s own tissue). The main advantages of choosing autologous reconstruction include a soft, natural breast mound that can better match a natural breast. Additionally, autologous reconstruction is associated with a lower long-term risk of surgical revision compared to implant-based reconstructions. Patient-reported outcomes measured using the BREAST-Q module indicate improved long-term patient satisfaction following autologous tissue reconstruction [2]. The deep inferior epigastric perforator (DIEP) flap remains the gold standard in autologous breast reconstruction [3], as it generally results in lower donor-site morbidity and optimal outcomes [1,4,5]. The DIEP flap (Figure 1) uses the same lower abdominal island of skin and fat as the pedicled transverse rectus abdominis myocutaneous (TRAM) flap, with the advantage of sparing the rectus abdominis muscle, thus resulting in a lower incidence of abdominal wall laxity and weakness, less postoperative pain, and a shorter recovery period [4,6-10].

However, no surgical procedure is without potential complications. DIEP flap complications include fat necrosis, partial or total flap loss, and abdominal wall laxity or hernia. In a series of 758 DIEP flaps performed for breast reconstruction, 6% of patients were returned to the operating room (OR) for flap-related problems [6]. Partial flap loss occurred in 2.5% of patients and total flap loss in less than 1% [6]. Other complications included fat necrosis (13%), seroma formation at the abdominal donor site (5%), and abdominal hernia (0.7%) [6]. As noted, several complications stem from poor flap perfusion. The current evidence suggests that the rate of perfusion-related complications with DIEP flaps is relatively high and highly variable [11,12], with several factors potentially playing a role, such as patient selection, surgical technique, perioperative fluid management, level of hemodynamic control, and perioperative use of inotropes and/or vasopressors. Hence, providing optimal perioperative management for fluid administration and hemodynamic goals may have a significant impact on the long-term viability of the DIEP flap.

DIEP flaps are typically performed under general anesthesia. Vasoactive agents (eg, phenylephrine) commonly used to counteract the hypotensive effects of general anesthetics are often avoided in flap surgery due to concerns over vasoconstriction, which have been proven in animal models to consistently reduce the pedicle artery blood flow and microvascular perfusion of the flap [13]. Although definitive evidence is lacking in humans, a retrospective investigation suggests a trend toward increased partial flap loss in patients who received vasopressors compared to patients who did not [14]. Conversely, certain inotropes (eg, dobutamine, dopexamine) may be beneficial in enhancing peripheral oxygen delivery through increased cardiac output (CO) and a direct peripheral vasodilatory effect [15].

In DIEP flap surgery, maintaining normovolemia is of particular interest, as hypovolemia may lead to tissue hypoperfusion and hypervolemia may result in tissue edema, both of which can ultimately cause poor flap oxygenation. Indeed, a retrospective analysis of 354 free flaps for breast reconstruction revealed that the extremes of crystalloid infusion significantly predicted postoperative complications [16]. Yet, in current clinical practice, perioperative fluid therapy is commonly prescribed using subjective criteria, leading to wide variations in the total volume of crystalloid administered perioperatively. Therefore, CO monitoring to guide intravenous fluid management as part of a goal-directed hemodynamic therapy algorithm could significantly benefit this patient population. Notably, this approach has been studied for many years in various settings and has been shown to modify inflammatory pathways and improve tissue perfusion and oxygenation [15,17,18]. Specifically, a prospective analysis of 104 DIEP flaps comparing fluid-guided therapy by CO monitoring versus central venous pressure (CVP) found that the fluid input was not different between groups; however, patients in the CVP group had a smaller fluid output (blood loss, urine output, etc) and were in greater positive fluid balance, whereas the CO monitoring group had a reduced anesthetic time (despite similar surgical time between groups) and spent a mean of 1.9 days less in the hospital [19]. No differences were observed concerning core temperature or flap complications [19]. These findings suggest that meticulous fluid management and tight hemodynamic control, combined with select inotropes, may optimize flap perfusion.

**Figure 1 figure1:**
[figure not shown]
Depiction of deep inferior epigastric perforator (DIEP) flap breast reconstruction surgery in which the lower abdominal island of skin and fat are used to form the tissue flap for breast reconstruction while sparing the rectus abdominis muscle. Although the muscle must be split to dissect out the perforating vessels, the muscle is not transferred. The deep inferior epigastric artery and vein, which provide the vascular supply for the free flap, are anastomosed to local recipient vessel using either the internal mammary or thoracodorsal arteries and veins. Image reproduced with permission from the Mayo Foundation for Medical Education and Research, all rights reserved.

Dobutamine (2 to 20 mcg/kg/min) is an inotrope widely used to treat cardiogenic shock and/or congestive heart failure. Its predominantly β-1 adrenergic receptor stimulatory effect increases inotropy and chronotropy and reduces left ventricular filling pressure. Dobutamine also has minimal β-2 adrenergic receptor effects, resulting in peripheral vasodilation. The net effect is increased CO and decreased systemic vascular resistance, with a generally imperceptible effect on blood pressure [20].

### Purpose and Hypothesis

The purpose of this trial is to evaluate the effects of perioperative hemodynamic therapy (guided by CO monitoring) on tissue oxygenation during and after DIEP flap breast reconstruction surgery. We hypothesize that a low-dose, perioperative dobutamine infusion combined with goal-directed fluid therapy guided by CO monitoring will improve flap perfusion, and thus oxygenation, in patients undergoing DIEP surgery.

### Objectives and Outcome Measures

The main objective is to determine whether the use of minimally invasive CO monitoring to guide intravenous fluid administration, combined with low-dose dobutamine infusion (via a treatment algorithm), will increase overall tissue oxygenation in patients undergoing DIEP flap surgery. The primary outcome is tissue oxygenation, measured via near-infrared spectroscopy (NIRS), 45 minutes following vascular reanastomosis of the DIEP flap within the perfusion zone farthest from the perforator vessels. This zone is the most vulnerable surgical area to ischemia and therefore the most likely to reflect the potential benefits of the proposed intervention. In the case of bilateral DIEP flaps, this zone will be assessed in both the left and right breasts. The zonal blood supply for DIEP flaps is depicted by Holm (Figure 2) [21]. Zone 1 includes the perforator vessel and is thus the most reliably perfused portion of the flap, while any flow across the midline can be less reliable than ipsilateral flow depending on the location of the perforators in zone 1. As aforementioned, the primary outcome will be tissue oxygenation within the zones farthest from the perforator vessels.

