### Participants and Recruitment

#### Overview

Patients scheduled for elective unilateral or bilateral delayed or immediate DIEP flap surgery at a medium-sized academic center will be recruited. Eligible patients will be approached at their preoperative surgical visit with the plastic surgeon ([name]). If patients are willing to participate, a research team member will obtain written informed consent after their assessment by the attending surgeon (Multimedia Appendix 1). In all cases, the anesthesiologist will be made aware of the patient’s potential study involvement should there be any medical reasons warranting study exclusion.

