### Study Design, Randomization, and Blinding

#### Overview

This is a prospective RCT. A total of 40 participants will be randomized to one of 2 groups (n=20 per group) using a computer-generated randomization prepared by the institutional biostatistician. Patient randomization will be concealed in envelopes and opened only by the research staff (not otherwise involved with data collection) and/or the attending anesthesiologist prior to anesthesia induction. Blinding will be maintained until study completion and verification that all outcome data have been successfully collected for all study participants.

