#### Surgical Procedure

Patients will be marked in the preoperative holding area for an abdominal-based free-flap breast reconstruction. All procedures are planned as a DIEP reconstruction. For most flaps, the goal is to include 1 to 3 perforators to optimize perfusion. In some cases, the DIEP flap may be converted to a muscle-sparing flap to achieve adequate arterial inflow and venous outflow to the tissue flap. Because the primary outcome is to look at perfusion of the flap most distant from the perforating vessels, in most cases, unilateral breast reconstructions will be performed, and perfusion zones 1, 2, and 3 included, according to the Holm classification (Figure 2). However, in patients with bilateral reconstructions, only Holm zones 1 and 2 will be included in a single flap. The supplying deep inferior epigastric vessels will be harvested at the level of the iliac artery and vein, and a microvascular anastomosis will be performed with the internal mammary artery and vein under a surgical microscope. A single artery and vein will be routinely anastomosed.

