#### Statistical Analysis

Data will be entered into REDCap (Research Electronic Data Capture; version 10.6.12; Vanderbilt University). Upon study completion, the data will be exported to SPSS software (version 29.0; IBM Corp) for analysis. Descriptive analyses, including mean, SD, median, and interquartile range for continuous data, as well as frequencies and percentages for categorical data, will be completed for all demographic and surgical characteristics and study outcomes. The underlying distributions of all continuous data will be assessed for normality using the Shapiro-Wilk test. Tissue oxygenation will be compared using independent sample *t* tests if the data are normally distributed and the Mann-Whitney *U* test in the event that they are not. Secondary outcomes will be compared between the 2 groups using the Fisher exact or Pearson chi-square tests (as appropriate depending on cell sizes) for categorical data and independent samples *t* tests (or the Mann-Whitney *U* test depending on the underlying distribution) for continuous data. Intent-to-treat analyses will not be conducted, and no adjustments will be made for missing data. Repeated measures analysis of variance (ANOVA), with the group as a factor, will be used to compare the tissue oxygenation over time (baseline, 1, 2, 4, and 8 hours postoperatively, along with baseline and postoperative day 1 and day 2 data). *P*<.05 will be used as the criteria for statistical significance, and no adjustment will be made for multiple comparisons. The possibility of a type I error will be acknowledged, and the actual *P* values will be presented for all comparisons.

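### The primary outcome gives two readings in bilateral patients and one in unilateral patients, from different perfusion zones, but the stated two-sample test defines no single value per patient and takes no account of zone

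*Protocol article*

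**What the plan says.** Four parts of the protocol article bear on this point.

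- **Objectives and Outcome Measures** sets the primary outcome as near-infrared tissue oxygenation "45 minutes following vascular reanastomosis of the DIEP flap within the perfusion zone farthest from the perforator vessels". For bilateral surgery it adds: "In the case of bilateral DIEP flaps, this zone will be assessed in both the left and right breasts".
- **Surgical Procedure** says that "in most cases, unilateral breast reconstructions will be performed, and perfusion zones 1, 2, and 3 included", but "in patients with bilateral reconstructions, only Holm zones 1 and 2 will be included in a single flap". The farthest zone is thus zone 3 in the usual unilateral flap and zone 2 in each flap of a bilateral patient.
- **Participants and Recruitment** admits both kinds of operation ("Patients scheduled for elective unilateral or bilateral delayed or immediate DIEP flap surgery") and gives no cap on, or expected share of, bilateral cases.
- **Statistical Analysis** gives the primary comparison: "Tissue oxygenation will be compared using independent sample" t tests, with the Mann-Whitney U test if the data are not normal.

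Allocation is described under Study Design, Randomization, and Blinding as 20 patients per group, "using a computer-generated randomization prepared by the institutional biostatistician". The article gives no rule for combining left and right readings and mentions neither stratification nor adjustment by laterality or zone.

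**The concern.** A two-sample t test or Mann-Whitney test needs one independent value per patient. The outcome definition supplies two for some patients. The left value, the right value, their mean, the worse side, or every flap as its own row would all fit the text, and the choice could be made after the data are seen.

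The second issue is zone. The farthest zone was chosen because it is the most vulnerable to ischaemia, so readings from zones 2 and 3 may well differ in level. If they do, the pooled outcome carries extra variance, and an uneven split of bilateral patients between two arms of 20 moves the treatment estimate.

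At stake are the error rate of the only primary test (if flaps are treated as independent), its power, and how far one realised result depends on which arm drew more bilateral cases.

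**Working it through.** **Inputs from the article.** 20 patients per arm. The Sample Size section uses a difference of 1.75 − 0.50 = 1.25 kPa, SD 1.0, α 0.05 (taken as two-sided) and 80% power, giving 11 per arm.

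**Assumptions, not in the article.** Bilateral share f = 0.2 to 0.5; left-right correlation ρ = 0.5 to 0.7; zone gap g = 0, 0.5 or 1 SD. All effects are in SD units, because the planning figures concern oxygen partial pressure, not the near-infrared reading.

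**The plan's own figure.** n = 2 × ((1.960 + 0.842)/1.25)² = 10.05, rounded up to 11. The stated figure reproduces (the t-based solution is 11.09). With 20 per arm, power at 1.25 SD is 97%, and 80% power is reached at 0.91 SD.

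**If every flap is entered as an independent value.** The variance is understated by the design effect D = [(1 − f) + 2f(1 + ρ)]/(1 + f), and the actual type I error is about 2 × [1 − Φ(1.96/√D)].

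| f | ρ | D | approximate type I error |
|---|---|---|---|
| 0.2 | 0.5 | 1.4/1.2 = 1.17 | 7.0% |
| 0.2 | 0.7 | 1.48/1.2 = 1.23 | 7.8% |
| 0.5 | 0.5 | 2.0/1.5 = 1.33 | 9.0% |
| 0.5 | 0.7 | 2.2/1.5 = 1.47 | 10.6% |

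Simulation with 20,000 runs per setting gives 7.1% to 10.8% over the same range. With the mean of the two sides as one value per patient, simulated error was 4.8-5.2% in all nine settings tried (25-75% bilateral, correlation 0.3-0.8).

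**If one value per patient is used but zone is ignored.** With a single reading per patient the variance is 1 + f(1 − f)g². With left and right averaged it is (1 − f) + f(1 + ρ)/2 + f(1 − f)g². Power of the two-sample t test with 20 per arm:

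| g | value used | SD | power at 0.91 SD | power at 1.25 SD |
|---|---|---|---|---|
| 0 | single reading | 1.00 | 80% | 97% |
| 0 | mean of sides | 0.94-0.99 | 81-85% | 97-98% |
| 0.5 | single reading | 1.02-1.03 | 78% | 96-97% |
| 0.5 | mean of sides | 0.97-1.01 | 80-83% | 97-98% |
| 1 | single reading | 1.08-1.12 | 71-74% | 93-95% |
| 1 | mean of sides | 1.05-1.08 | 73-76% | 94-96% |

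For example, with f = 0.5, ρ = 0.5, g = 1 and averaging: 0.5 + 0.375 + 0.25 = 1.125, SD 1.06, power 75% at 0.91 SD.

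**Chance imbalance.** With 8, 14 or 20 bilateral patients among 40 and unstratified 20/20 allocation, a between-arm difference of four or more has probability 24%, 32% or 34% (hypergeometric). With a 1 SD zone gap, four patients shift the estimate by 4/20 × 1 = 0.20 SD. This is the same variation that enlarges the SD in the table, seen after allocation; it is not a second loss.

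**Adjusting for laterality.** In simulation with one averaged value per patient and a 1 SD gap, adding laterality raised power at 0.91 SD from about 74-75% to about 80-84%, with type I error near 5%. With no gap it cost about 1 point.

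**The case against.** The strongest reply is that the patient is the unit throughout: the sample size counts cases per arm and the design section randomises 40 participants. Nothing says flaps will be separate observations. A reader might infer from the two-sided measurement and the plain test that the trial will run at 7-11% type I error. The article does not support that; the figure applies only if both flaps are entered as independent. This part of the objection stands.

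A reader might also infer that mixing zones biases the treatment effect. It does not: randomisation balances laterality on average, and the unadjusted standard error already carries the variation. Nor does the absence of any mention of stratification show that none was used.

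A zone gap is itself an inference. The article says flow across the midline can be less reliable, depending on where the perforators lie, and the zone figure is not available here. Measuring each flap at its own most vulnerable site is a coherent outcome. The 1 SD gap has no source, and 50% bilateral sits badly with a text that expects unilateral surgery in most cases. At the planning effect of 1.25 SD, power remains above 90% in every setting shown, so the point cannot be put as an underpowered trial.

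The remaining argument is that a combining rule can be left to a fuller document. That would carry weight if the article were silent on the analysis. But it fixes both the two-sided measurement and the test, and together these do not determine the primary analysis.

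**Conclusion.** The point holds as a gap in the primary analysis. Bilateral patients have no defined primary value, and the stated test takes no account of the zone that differs by type of operation.

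The type I error of roughly 7-11% is conditional on an analysis the article does not announce, and on 20-50% bilateral with correlation 0.5-0.7. With one value per patient the comparison is valid on average; what remains is a loss of precision and exposure to chance imbalance. With an assumed 1 SD zone gap, power is about 71-76% at 0.91 SD and about 93-96% at the planned 1.25 SD. With a 0.5 SD gap the loss is small.

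This should be fixed, but it does not threaten the trial's validity as described.

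**What to change.** Before unblinding, make these changes to the primary analysis:

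1. Define one primary value per patient: the single 45-minute reading in unilateral cases and the mean of the left and right readings in bilateral cases.
2. Compare groups with a linear model containing treatment and laterality (unilateral or bilateral, which stands for zone 3 or zone 2). An equivalent choice is a linear mixed model on all flap readings, with a random patient effect and laterality as a fixed effect.
3. Show the results by laterality descriptively, without a separate test.

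The cost is one degree of freedom, and about 1 point of power if the zones do not differ. No new measurement is needed. Laterality is not in the listed surgical characteristics, but it is known from the operation performed. The article reports that investigators were still blinded with 34 patients recruited; the change is clean only while that remains so.
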